#### Interim analysis

On account of safety concerns, an interim analysis will be performed when 50% of the patients are included in the study. In this analysis, we will compare the number of neonates with a 5- minute Apgar score < 7 and/or pHa < 7.05, the number of admissions to the NICU and perinatal death in both groups (all neonates that received oxygen in both suboptimal and abnormal CTG groups versus ‘conventional care’ group). If the interim analysis shows a significant difference, we will terminate the study. This interim analysis is performed exclusively for safety reasons; because the primary outcome measure (FHR) will not be analysed during the interim analysis and power analysis is based on the primary outcome, adjustment of the significance level is not required.

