### Statistical analysis

#### Sample size calculation

The study consists of two study groups: one group with suboptimal FHR patterns and one group with abnormal FHR patterns. We aim for the study to have 80% power and a level of significance of 0.05 in both groups. In one small, non-randomised study, a reduction in FHR decelerations (type II dips) of 50–100% was noted. Our present study is the only one to report FHR changes as a result of maternal hyperoxygenation. On the basis of available literature, we expect ≥ 50% improvement in the oxygen group and 0% in the control group in both suboptimal and abnormal FHR patterns [28]. We estimated a mean improvement of 50% with an SD of 50% in each group. A power analysis performed in G*Power 3.0.10 (Kiel University, Kiel, Germany) for a two-tailed Mann-Whitney *U* test (assuming that data will not be equally distributed) resulted in a sample size of 67 patients in each study group. We added an extra 20% to compensate for missing data. Because we have two separate study groups (suboptimal and abnormal FHR group), we need 162 patients to participate.

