#### Data analysis

IBM SPSS Statistics software (version 24; IBM, Armonk, NY, USA) will be used to perform statistical analysis of the study results. Assuming non-normal distribution, the primary clinical outcome will be analysed with a Mann-Whitney *U* test for differences between the intervention and control groups and a Wilcoxon matched-pairs test for changes within the same participant. When outcome data are found to be normally distributed, independent samples *t* tests (two-tailed) will be used to analyse differences between the intervention and control groups, and paired *t* tests will be used for changes within the same participant. Outcome measures will be calculated for the combined group and the subgroups of suboptimal and abnormal FHR tracings, as well as for small for gestational age (SGA, lower than 10th percentile) and appropriate for gestational age (AGA) neonates. In the intervention group, oxygen may not be applied, owing to practical concerns such as very quick progression of labour. Therefore, we will perform both per-protocol and intention-to-treat analyses. In the per-protocol analysis, parturients who actually received oxygen will be compared with those who did not receive oxygen. In addition, unjust inclusions will be excluded from this analysis.

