In this study, we focus on the foetal condition during the second stage of labour and short-term neonatal outcome. This implies that abnormalities in FHR patterns during the first stage of labour are not taken into account. We believe that the randomisation process will limit its influence. With regard to the neonatal period, we did not arrange long-term follow-up, because we do not expect any clinically relevant side effects that can be attributed to maternal hyperoxygenation. Besides, the sample size is too small to draw firm conclusions on long-term neonatal effects in this study.

Power analysis of the present study is based on the expected effect on the primary outcome measure, and the study is not powered to find any significant differences in Apgar score and umbilical cord blood gas values. In the power analysis, we used an expected improvement in deceleration depth and duration of 50%. On one hand, this value is based on small non-randomised studies and may be overestimated. On the other hand, those studies provide the only available data. Also, we believe it is unlikely that a limited improvement in deceleration depth and duration has clinical relevance. The sample size is calculated for each of the subgroups of suboptimal and abnormal FHR tracings. We believe it is important to assess the effect of the intervention in these subgroups because foetuses with lower initial pO_2_ levels may profit more from maternal hyperoxygenation [29].

Regarding the subgroups of AGA and SGA infants, we did not increase our sample size to reach an adequate number of participants in the SGA group. Nevertheless, we find it interesting to investigate whether there is a different effect of maternal hyperoxygenation in SGA infants compared with AGA infants.

Because of organisational challenges, it is not possible to conduct a double-blind trial. Hence patients and delivery room staff are not blinded to the patient’s allocation to a study group, which may lead to observer bias. However, analysis of FHR tracings will be done using a computerised algorithm, to minimise bias, and the investigators judging the CTGs and secondary outcome measures are blinded to the study arm.

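### The interim safety rule has no direction and groups neonates by oxygen received, and it would often miss moderate harm at half enrolment

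*Protocol article*

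**What the plan says.** The Interim analysis section of the protocol article schedules a single look: "an interim analysis will be performed when 50% of the patients are included in the study". The outcomes set against each other are these: "neonates with a 5- minute Apgar score < 7 and/or pHa < 7.05, the number of admissions to the NICU and perinatal death". As for who is compared, the section has "all neonates that received oxygen in both suboptimal and abnormal CTG groups versus" those given usual care. The consequence is fixed: "If the interim analysis shows a significant difference, we will terminate the study". The purpose is fixed too: "This interim analysis is performed exclusively for safety reasons".

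Two other places bear on this. The Data analysis section says: "In the intervention group, oxygen may not be applied, owing to practical concerns such as very quick progression of labour". The Discussion concedes, of the whole trial, that "the study is not powered to find any significant differences in Apgar score and umbilical cord blood gas values". The article gives no expected rates of these neonatal outcomes in its own population, and names no test or level for the interim comparison.

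**The concern.** Three features of the stated rule work against its purpose.

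- **Direction.** A safety look should end the trial when oxygen appears to do harm. The rule as worded reacts equally to fewer events on oxygen and leaves no discretion in that case.
- **Analysis set.** Women allocated to oxygen who deliver too quickly to receive it drop out of the oxygen group. The section does not say whether they are left out or counted elsewhere. Their labours differ from the rest, and speed of delivery may be related to the neonate's condition, so the two groups are no longer those that randomisation formed.
- **Sensitivity.** Significance is the trigger at half the size of a trial that its authors call too small for most of these outcomes. A null interim could be taken as reassurance that it cannot give.

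At stake is whether mothers and foetuses continue to be exposed on the strength of a comparison that would often miss moderate harm.

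**Working it through.** **Size at the interim.** The article gives no power figure for the interim rule, so there is none to reproduce. The sample size section gives 67 per study group plus 20%: 67 × 1.2 = 80.4, rounded up to 81; 2 × 81 = 162. Half is 81, that is 40 or 41 per arm. The Abstract gives 116; half is 58, or 29 per arm. Both are carried below.

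**Assumptions.** Event rates are assumed. The test is assumed to be a two-sided Fisher exact test. The level is taken as 0.05, which the article states for the primary outcome: "We aim for the study to have 80% power and a level of significance of 0.05 in both groups". Each outcome is taken singly.

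**Formula.** For a oxygen and c control neonates with true rates p₁ and p₀:

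P(stop for harm) = Σ Bin(i; a, p₁) × Bin(j; c, p₀), summed over all (i, j) with Fisher p < 0.05 and i/a > j/c.

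P(stop for benefit) is the same sum with i/a < j/c.

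**Events needed on oxygen to reach p < 0.05**

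| Oxygen/control n | 0 control events | 1 | 2 |
|---|---|---|---|
| 29/29, 40/40, 41/40 | 6 | 8 | 9 |
| 40/41 | 5 | 7 | 8 |

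**Probability of stopping for harm**

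| Control → oxygen rate | 29/29 | 40/40 | 40/41 | 41/40 |
|---|---|---|---|---|
| 2% → 4% | <1% | <1% | 1% | <1% |
| 5% → 10% | 2% | 4% | 8% | 5% |
| 5% → 15% | 9% | 18% | 28% | 20% |
| 10% → 20% | 9% | 16% | 23% | 18% |
| 10% → 30% | 35% | 53% | 62% | 56% |

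For comparison, 80% power needs 435 per arm for 5% → 10% and 199 per arm for 10% → 20%.

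**Several outcomes.** Three comparisons are listed. If any one can trigger a stop, the total probability is at most the sum of the three. If all three rates doubled from 5% to 10%, that bound is 3 × 4.2% ≈ 13% at 40/40 and 3 × 8.4% ≈ 25% at 40/41. The rule remains weak.

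**Choice of test.** An uncorrected chi-square test at 40/40 gives 14%, 35% and 25% for 5% → 10%, 5% → 15% and 10% → 20%.

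**Stopping for benefit.** If oxygen cut a rate from 20% to 5%, the literal rule would stop with probability 22% at 29/29, 41% at 40/40, 44% at 40/41 and 53% at 41/40. For a cut from 10% to 5% at 40/40 it is 4%.

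**A harm-only alternative, for illustration.** A one-sided Fisher test at 0.10 with 40/40 detects 5% → 10% with probability 17%, 5% → 15% with 43% and 10% → 20% with 38%. With no true difference it flags harm in 2% (5% in both arms) to 5% (10% in both arms).

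**Analysis set.** No arithmetic applies, because the expected number of intervention-arm women without oxygen is not given. The Data analysis section plans both intention-to-treat and per-protocol analyses of the trial results; the Interim analysis section describes only a comparison by oxygen received.

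**The case against.** The strongest reply is that context settles the direction: the section opens and closes on safety, so a harm reading is natural and a short clarification cures it. That is fair, and it is one reason for the moderate grade. The operative sentence still prescribes termination for either direction.

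The oxygen-received wording may be shorthand for the intervention arm, since the phrase also explains that the two CTG strata are pooled. Exposure-based comparison is, besides, a common choice for safety. Both points are reasonable. If it is shorthand, the text should say so; if it is meant, it belongs beside a comparison by allocated arm. The size of any bias cannot be worked out from the article.

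Low power for Apgar score and cord gases is openly disclosed, and nothing in the section claims that a non-significant interim shows safety. That stands. The disclosure does not, however, tell those acting on the interim how little it can exclude.

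Four stronger readings are tempting but not supported:

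- *The rule can hardly detect any harm.* A rise from 10% to 30% is caught 53–62% of the time at about 40 per arm, and the article gives no event rates that would establish how rare the outcomes are.
- *Five deaths against none would not stop the trial.* With Fisher's test this is true at 40/40 (p = 0.055), but at 40 oxygen and 41 control p = 0.026 and the trial would stop. An uncorrected chi-square gives p = 0.021 at 40/40.
- *Significance is the only safeguard.* Staff may overrule the protocol for an individual patient, the schedule figure's legend refers to SAE and SUSAR items, and the full protocol is not shown.
- *Stopping for benefit would leave the FHR question unanswered.* On the article's planning inputs (50% against 0%, SD 50%, so a standardised difference of 1), a t test needs about 17 per arm. A Mann-Whitney test needs about 17/0.955 ≈ 18 to 17/0.864 ≈ 20. The interim would already hold 29 or about 40 per arm overall. Precision would be lost, above all within the strata, but not necessarily the answer.

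**Conclusion.** The point holds in a bounded form and is a should-fix. The missing direction and the grouping by oxygen received are in the text itself and need no assumption. The insensitivity to moderate harm rests on assumed event rates, an assumed Fisher test at two-sided 0.05 and one outcome at a time. Doubling a 5% rate, or raising 5% to 15% or 10% to 20%, would stop the trial in at most 28% of cases at about 40 per arm and at most 9% at 29 per arm. Under a chi-square test at 40/40 the highest of these is 35%, so the conclusion does not depend on the choice of test. How likely a stop for benefit is depends heavily on the true effect: 41% for 20% → 5% but 4% for 10% → 5%, both at 40/40. The article's own hypothesis expects no difference in Apgar score or cord pH.

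**What to change.** In the Interim analysis section:

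1. State that the interim tests for harm on oxygen only, so that a favourable difference does not trigger termination.
2. Make the comparison by allocated arm the main interim analysis, with oxygen received as a supporting analysis, and say where intervention-arm women without oxygen are counted.
3. Name the test and its level, say how the three outcome comparisons combine into one decision, and give the probability of detecting stated degrees of harm at the actual interim size. Add that a non-significant interim is not evidence of safety.

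This is wording plus a short calculation; no extra patients or data are needed. A less stringent one-sided level is an option for the sponsor to weigh, not a required value. At one-sided 0.10 with 40 per arm, detection of 5% → 15% rises from 18% to 43%, at the cost of 2–5% false alarms. Even then more than half of such harms would be missed, which is why the detection probability should be stated whichever level is chosen.

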### Public disclosure and publication policy

All investigators agree to publish the study results in an international peer-reviewed journal, even if the results do not correspond to the hypothesis as stated in the Methods section of the protocol. The results will be offered for publication after all the investigators agree on the content of the article. The full protocol (version 8, dated 1 March 2017) is available upon request.

## Discussion

This study is the first RCT to investigate the effect of maternal hyperoxygenation for foetal distress during labour [18, 33]. So far, the effects of supplemental oxygenation in the presence of FHR abnormalities have been investigated only in small, non-randomised studies. Because of the lack of concrete results from clinical trials, it is hard to compare the beneficial effects of maternal hyperoxygenation with the potential side effects. As a result, recommendations on the use of this intervention for foetal distress in international guidelines are non-uniform [20]. Thus, the results of this study will help to filling an internationally recognised ‘research gap’.

We believe patient safety is carefully addressed in this study, and ethical concerns are limited. One of the major concerns of administering high fractions of oxygen is the increase in free oxygen radicals. Whether this has a clinical effect remains unclear. We excluded from this study all patients with a higher a priori risk of exposure to increased free oxygen radical levels.

Both practical and safety issues led to limitations of this study. An important limitation is the primary outcome measure. We recognise that changes in FHR as a primary outcome measure are not optimal, because FHR does not accurately reflect foetal oxygenation and acid-base balance [60, 74, 75]. However, we believe this is the best available method to record changes in the foetal condition during labour. Furthermore, we assume that if no beneficial effect on FHR can be shown, an improvement in neonatal outcome is unlikely. Ideally, neonatal outcome measures such as Apgar score and umbilical cord pH are the outcome measures of first choice. However, a study with appropriate power to address these outcome measures would need a very large sample size. Because the potentially harmful effects have not been investigated properly yet, we chose not to expose a large group of women and their foetuses to this intervention. If a positive effect on FHR pattern without severe side effects can be confirmed by this study, we will perform a larger multicentre RCT to investigate the effect on Apgar score and cord blood gas values.

In this study, we focus on the foetal condition during the second stage of labour and short-term neonatal outcome. This implies that abnormalities in FHR patterns during the first stage of labour are not taken into account. We believe that the randomisation process will limit its influence. With regard to the neonatal period, we did not arrange long-term follow-up, because we do not expect any clinically relevant side effects that can be attributed to maternal hyperoxygenation. Besides, the sample size is too small to draw firm conclusions on long-term neonatal effects in this study.

Power analysis of the present study is based on the expected effect on the primary outcome measure, and the study is not powered to find any significant differences in Apgar score and umbilical cord blood gas values. In the power analysis, we used an expected improvement in deceleration depth and duration of 50%. On one hand, this value is based on small non-randomised studies and may be overestimated. On the other hand, those studies provide the only available data. Also, we believe it is unlikely that a limited improvement in deceleration depth and duration has clinical relevance. The sample size is calculated for each of the subgroups of suboptimal and abnormal FHR tracings. We believe it is important to assess the effect of the intervention in these subgroups because foetuses with lower initial pO_2_ levels may profit more from maternal hyperoxygenation [29].

Regarding the subgroups of AGA and SGA infants, we did not increase our sample size to reach an adequate number of participants in the SGA group. Nevertheless, we find it interesting to investigate whether there is a different effect of maternal hyperoxygenation in SGA infants compared with AGA infants.

Because of organisational challenges, it is not possible to conduct a double-blind trial. Hence patients and delivery room staff are not blinded to the patient’s allocation to a study group, which may lead to observer bias. However, analysis of FHR tracings will be done using a computerised algorithm, to minimise bias, and the investigators judging the CTGs and secondary outcome measures are blinded to the study arm.

To investigate the effect of maternal hyperoxygenation in the presence of foetal distress on the release of free oxygen radicals, MDA is estimated in umbilical cord blood. MDA is the peroxidation product of membrane polyunsaturated fatty acids. We chose to measure this marker for oxidative stress because it was used in prior studies performed during labour and it is related to vaginal birth, non-reassuring FHR tracings, maternal hyperoxygenation and acidaemia in arterial cord blood [36, 37, 39, 41]. We realise that differences in values in umbilical cord blood may be confounded by mode and duration of delivery; therefore, we will correct the results for the mode of delivery. A practical ground on which to choose this marker is that it is the only marker for oxidative stress that can be estimated accurately in Dutch laboratories. In the intervention group, oxygen administration will be continued until delivery to enable analysis of its effect on cord blood gas values and MDA.

Despite some important limitations of this study, we believe this is the best possible way to perform a study while restricting safety issues. If the results do not show any improvement in FHR, we believe that maternal hyperoxygenation should not be used as a treatment for foetal distress. However, if a beneficial effect is demonstrated, we will design a multicentre RCT to investigate the effect on neonatal outcome.

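### The SGA-versus-AGA question is about a difference in oxygen effect, but the stated analysis tests each subgroup separately and does not compare the effects (minor, exploratory)

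*Protocol article*

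**What the plan says.** Data analysis in the protocol article names two kinds of test. For the between-arm comparison it says "Assuming non-normal distribution, the primary clinical outcome will be analysed with a Mann-Whitney" U test, with a t test if the data prove normal. For change within a participant it names a Wilcoxon matched-pairs or paired t test. Outcomes are then to be calculated for the combined group and for the two FHR subgroups, "as well as for small for gestational age (SGA, lower than 10th percentile) and appropriate for gestational age (AGA) neonates".

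The Discussion gives the purpose of the last split: "we find it interesting to investigate whether there is a different effect of maternal hyperoxygenation in SGA infants compared with AGA infants". It also concedes that "we did not increase our sample size to reach an adequate number of participants in the SGA group".

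The article names no interaction term, and no direct comparison of the oxygen effect in SGA infants with that in AGA infants. It does not give the share of SGA infants expected. It sets no rule for concluding that the effects differ.

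**The concern.** The null hypothesis behind the question is that oxygen has the same effect in SGA and AGA infants. A between-arm test run among SGA infants has a different null, that oxygen has no effect in them, and likewise for AGA. A paired test within a subgroup has the null of no change over time. No pair of such tests addresses equality of the two effects.

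The mismatch matters because the subgroups will probably be very unequal in size. With the same true effect in both, the larger one can easily reach significance while the smaller one does not. A reader who takes that pattern as the answer would conclude that SGA infants respond differently when only the numbers differ.

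**Working it through.** **Inputs from the article.** Sample size calculation: "We aim for the study to have 80% power and a level of significance of 0.05 in both groups", two-tailed; "we expect ≥ 50% improvement in the oxygen group and 0% in the control group"; SD 50%. The planned effect is therefore 50/50 = 1.0 SD. The total is 162 there and 116 in the Abstract.

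**The plan's own total.** 67 × 1.2 = 80.4, rounded up to 81 per FHR group; 81 × 2 = 162. This step reproduces. The 67 does not: at 1.0 SD a Mann-Whitney test needs about 18 per arm, 36 per FHR group, and 67 appears as a per-arm figure only at 0.5 SD. That is a separate point, but it is a reason to show 0.5 SD as well as 1.0 SD here.

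**Assumptions.** 1:1 allocation, normal outcomes, the same true effect in both subgroups, and an SGA share of 10% with a range of 5% to 20%. The cut-off "lower than 10th percentile" defines SGA. It does not give the SGA share among women randomised for a suboptimal or abnormal trace.

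**Subgroup sizes.** At N = 162 there are 81 per arm. At 10%, 162 × 0.10 / 2 = 8.1, so about 8 SGA and 73 AGA per arm.

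**Chance that the verdicts disagree.** With simulated Mann-Whitney power P_S in SGA and P_A in AGA (two-sided 0.05),

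P(disagree) = P_A(1 − P_S) + P_S(1 − P_A).

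- 1.0 SD: 1.000 × (1 − 0.430) + 0.430 × 0 = 0.57.
- 0.5 SD: 0.831 × (1 − 0.156) + 0.156 × (1 − 0.831) = 0.701 + 0.026 = 0.73. Repeated simulations gave 72% to 75%.

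| N | SGA share | SGA / AGA per arm | Common effect | P_S | P_A | Disagree |
|---|---|---|---|---|---|---|
| 162 | 5% | 4 / 77 | 1.0 SD | 0.144 | 1.000 | 86% |
| 162 | 10% | 8 / 73 | 1.0 SD | 0.430 | 1.000 | 57% |
| 162 | 15% | 12 / 69 | 1.0 SD | 0.593 | 1.000 | 41% |
| 162 | 20% | 16 / 65 | 1.0 SD | 0.755 | 1.000 | 24% |
| 162 | 10% | 8 / 73 | 0.5 SD | 0.156 | 0.831 | 73% |
| 162 | 20% | 16 / 65 | 0.5 SD | 0.247 | 0.796 | 65% |
| 162 | 10% | 8 / 73 | 0.25 SD | 0.078 | 0.306 | 34% |
| 116 | 10% | 6 / 52 | 1.0 SD | 0.297 | 0.998 | 70% |
| 116 | 10% | 6 / 52 | 0.5 SD | 0.103 | 0.684 | 65% |

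A second run at 15% and 1.0 SD gave 38%. In nearly all the disagreements AGA is significant and SGA is not.

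**The direct contrast.** Take D = (oxygen − control in SGA) − (oxygen − control in AGA). At N = 162 and a 10% share,

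SE(D) = SD × √(2/8 + 2/73) = SD × √0.2774 = 0.527 SD.

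Under a common effect, a test of D rejects in about 5% of simulated trials. The half-width of its 95% interval is 1.96 × 0.527 = 1.03 SD, or about 52 percentage points at an SD of 50%. Its power for a true difference of 1.0 SD is Φ(1/0.527 − 1.96) = Φ(−0.06), about 48%. For 0.5 SD it is about 16%.

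**The case against.** The strongest reply is that this is a condensed article. A full protocol (version 8) is available on request, and the model for an exploratory subgroup comparison could be set out there. This stands to the extent that the point can be made only about the article. It does not dispose of it, because the article states both the question and the tests, and the two do not match.

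A reader might infer that the investigators intend to declare a difference when one subgroup is significant and the other is not. The text does not say so. It says outcomes will be calculated for each subgroup and that the comparison is of interest. The disagreement rates above are therefore what would follow from that reading. They are not the error rate of a stated rule.

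A reader might also infer that split verdicts are the usual result. That holds for a share near 10% and effects of 0.5 to 1.0 SD. It fails at the planned 1.0 SD and 162 women once the share is about 15% or more, and for a small effect such as 0.25 SD.

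Finally, the Discussion remarks that foetuses with lower initial pO2 may benefit more, and it is tempting to argue that a wrong SGA conclusion would misdirect the later multicentre trial. The pO2 remark justifies the suboptimal and abnormal FHR subgroups and is not about SGA. The later trial is made to depend on a favourable FHR result, not on an SGA finding.

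The authors do disclose that the SGA group was not sized for this comparison. That is a fair caution about power, but it does not change which null is tested.

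**Conclusion.** The point holds in limited form. The article asks whether the oxygen effect differs between SGA and AGA infants, and the tests it names cannot answer that. If the separate results were compared by significance, identical effects would give opposite verdicts in about 57% (1.0 SD) to 75% (0.5 SD) of trials at 162 women and a 10% SGA share, and in 24% to 86% at 1.0 SD over shares of 5% to 20%. These figures rest on an SGA share that the article does not give, on normal outcomes and on equal allocation. The issue is minor: the comparison is exploratory, and neither the primary analysis nor any stated trial decision depends on it.

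**What to change.** In Data analysis, add a sentence saying that the SGA-versus-AGA question will be answered by one treatment-by-SGA contrast on the FHR change, reported as the difference in oxygen effect with its 95% confidence interval and labelled exploratory. Show the SGA and AGA estimates beside it, each with a confidence interval. Name the interval method in advance. With about 8 SGA women per arm, a bootstrap interval for skewed data may itself be unreliable.

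The cost is one sentence and one extra model. Birth weight, gestational age and infant sex are already recorded under Other study endpoints and parameters. The downside is an interval of roughly ±1 SD at a 10% share, so the answer will probably be inconclusive. The contrast keeps the false-difference rate near 5% but does not cure the low power.
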